## Methods

### Participant recruitment

Participants will be recruited from district health clinics in the local area. Potential participants will be signposted to phone or text a study team member (English and Chichewa-speaking) if they are interested in participating, and will be invited to an information meeting. Passive recruitment methods will allow participants to freely participate without feeling pressured by direct solicitation, as identified in the EHPC acceptability study
^
18
^.

### Inclusion criteria

Aged 25 to 45 years oldFluent in spoken and written Chichewa or EnglishAble to give informed written consentAccess to a functional mobile phoneEstablish on antiretroviral therapy for ≥2 years (if PLHIV)Viral load below the lower limit of detection (<LDL) at screening (if PLHIV)CD4 count over 350 cells/mm³ at screening (if PLHIV)

### Exclusion criteria

HIV-associated hospitalisation and/or treatment for major illness in preceding 2 yearsCurrently under investigation for, or experiencing HIV-associated weight-loss, chronic diarrhoea, chronic cough, or another unexplained symptomPrevious illness caused by pneumococcusAdditional condition or medication impairing immune response or increasing risk of pneumococcal diseaseLiving in close contact with an individual vulnerable to pneumococcal disease (e.g. child under 5 years old, adults aged over 65 years, pregnant woman)Allergy or intolerance to penicillinAcute illness in 7 days preceding inoculationAntibiotic course in last 2 weeks (excluding prophylactic antibiotics in PLHIV)Pregnant or trying to conceiveInvolved in another clinical study (unless observational or in follow-up)Current regular cigarette smoking (5+ cigarettes per week)Natural carrier of pneumococcus serotype 6B at screening visitParticipants without a guardian

### Determination of colonisation

Pneumococcal colonisation will be assessed by conventional microbiological culture from nasal washes obtained from participants, and also confirmed by molecular methods (lytA polymerase-chain reaction-based methods). Pneumococcal colonisation is defined as the detection of pneumococcus serotype 6B by microbiological culture in nasal wash samples at any of the time points on days 2, 7, 14 and 21 post-inoculation, as previously described
^
19
^. The density of colonisation will be measured by classical microbiological culture and molecular methods.

### Sampling methods

Sampling methods used in this study have been successfully used during the PCV13 study at MLW, and are well-tolerated by participants
^
2,
20
^.

**
*Nasosorption:*
** An absorptive strip is held inside the nose for 3 minutes to collect concentrated nasal lining fluid.

**
*Nasal wash:*
** Five millilitres of sterile saline solution are instilled per naris with the participant in a semi-recumbent position. Participants are instructed to close their soft palate and hold the saline in the nares for a few seconds before leaning forward to allow the fluid to drip into a sterile Galli pot.

**
*Nasal curettage:*
** The cup-shaped end of a plastic, single-use rhinoprobe is grazed along the lower nasal turbinate of each nostril to collect nasal cells.

**
*Throat swab:*
** Simple posterior pharyngeal swabbing on a dry swab for viral co-infection testing.

**
*Venepuncture:*
** Venepuncture will be performed to ensure participants are fit to participate, to evaluate peri-inoculation serum levels of commonly used antibiotics, and to evaluate peripheral blood immune dynamics.

**
*Saliva:*
** salivette held for saturation or a spit in the tube.

### Safety monitoring

This will be the first CHIM study in PLHIV and participant safety is paramount. Experimental pneumococcal carriage is expected to be a benign event due to the pervasiveness of natural pneumococcal carriage in PLHIV and the low carriage to disease ratio. In the unlikely event that invasive pneumococcal disease develops in a study participant, robust safety monitoring will identify signs of invasive disease early and enable immediate treatment. Participants will be housed in study accommodation for the first three days following inoculation, as invasive disease tends to occurs early during carriage acquisition. Participants will have a symptoms-review and vital-signs check at every study visit. Any abnormalities will trigger a formal clinical review by a study doctor. In between study visits, participants will have phone contact with the study team to establish that they are well and apyrexial. An escalation protocol is established if participants are not contactable. An on-call doctor is available for participants 24/7 and participants are given written and verbal instruction on when and how to contact the doctor. All participants will be required to have a mobile phone, and will be issued a power-bank to keep their phone charged during power-outages. Participants will be issued an antibiotic course at the point of experimental inoculation and will be instructed to keep them on their person, and on when/if to take them. The pneumococcal isolate used during experimental inoculation is microbiologically and genetically confirmed antibiotic-susceptible. Participants will have the relevant safety information written in English and Chichewa on laminated, pocket-sized cards.

### Termination of carriage

Participant exhibiting pneumococcal carriage at any point during the study will be advised to commence a 3-day course of amoxicillin at study-end.

### Immunological measurements

Surface antigen staining of nasal cells will occur in real-time within 4 hours of collection to characterise the major nasal cell populations and their frequency at different time points of the study. Nasal fluid will be stored and will be analysed in batches using a commercial multiplex cytokine assay. Serotype-specific immunoglobulin G and A concentrations will be evaluated in blood, nasal wash and saliva respectively using antibody enzyme-linked immunosorbent assay (ELISA). Bulk RNA analysis will be performed on a subset of nasal samples, and single-cell sequencing will be performed on a small number of nasal cells collected using nasal swabs. Similar immune evaluations will be performed on blood to determine whether immune processes are local to the nasal mucosa, or from systemic spill-over.

### Sample size calculation

The study will recruit 75 PLHIV and 75 HIV-negative controls aged 25–45 years old. The sample size is based on 50% carriage rate following inoculation in HIV-negative controls
^
17
^, and a 50% greater carriage rate amongst PLHIV based on community carriage point-prevalence
^
21
^. 132 participants (66 per group) will be required to achieve 80% power with p=0.05 so 150 participants will allow for some participant drop-out.

### Statistical analysis

Descriptive statistics will be used to describe group characteristics and to describes rate of pneumococcal carriage in both groups. Pneumococcal carriage rate will be described by area-under the curve of carriage density over the duration of follow up, and as a binary carriage positive (at any time) compared to carriage negative. Natural carriage and baseline serum concentrations of commonly used antibiotics (e.g. cotrimoxazole) will be included as a variable in the regression. Two-tailed comparisons will be performed to evaluate density and activation of immune cell populations, and immunoglobulin concentrations between those who become colonised with pneumococcus and those who do not in PLHIV and HIV-negative controls. Paired comparisons will be performed to compare density and activation of immune cell populations before and after pneumococcal inoculation. Multiple comparisons will be adjusted for using Benjamini-Hochberg or Bonferroni methods
^
22
^.

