### Study hypotheses

PLHIV will exhibit higher carriage rate and density than HIV-negative controls following experimental pneumococcal inoculation.PLHIV will have perturbed mucosal and systemic immunity in response to experimental pneumococcal inoculation, compared to HIV-negative controls, which will predispose them to pneumococcal carriage.

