### Participant recruitment

Seventy-five HIV-negative adults and 75 PLHIV aged 25 to 45 years old.

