** Written consent will be obtained at this visit. A questionnaire will be conducted to ensure understanding of the study. Clinical screening will include a focused clinical history, a targeted clinical examination involving auscultation of the lung fields and heart sounds, blood sampling, a HIV antigen test if indicated, and a urinary pregnancy test if female. Blood samples will be obtained for full blood count, renal panel, and a HIV viral load and CD4 T cell count (if indicated) to evaluate participants’ fitness to participate in the study. Nasal cell and fluid samples and blood samples will be taken at this screening study visit to identify existing pneumococcal carriage, and to evaluate humoral and cellular immune markers. Participants naturally colonised with serotype 6B will not be eligible to continue in the study. Natural carriage with any other serotype can continue in the study. Should any previously unrecognised abnormality be identified during the screening visit, this will be explained to the individual, and appropriate investigations and follow-up will be arranged by the study team. Further participation will be determined at the discretion of the study doctor dependent on the nature of the abnormality detected. Eligible participants will be scheduled for their inoculation visit within 7 days of screening.

**
*Inoculation visit (study visit 2):*
** Participants will be inoculated with a microbiologically and genetically confirmed antibiotic-susceptible

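### The regression comparing carriage and density between PLHIV and HIV-negative controls names two covariates but not age or sex, although the groups are not randomised and both variables are known at screening

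*Protocol article*

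**What the plan says.** Study hypotheses states the between-group expectation: "PLHIV will exhibit higher carriage rate and density than HIV-negative controls following experimental pneumococcal inoculation". Participant recruitment, under Study protocol, gives the groups as "Seventy-five HIV-negative adults and 75 PLHIV aged 25 to 45 years old". The Methods section on recruitment describes passive recruitment from local district health clinics. The article states no matching, stratification or balancing by age or sex.

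On analysis, Statistical analysis says "Descriptive statistics will be used to describe group characteristics". It then summarises carriage in two ways: area under the curve of density, and a binary indicator of carriage at any time. The next sentence is the one that matters here: "Natural carriage and baseline serum concentrations of commonly used antibiotics (e.g. cotrimoxazole) will be included as a variable in the regression". It does not name the outcome of the regression; from its position, I read it as the carriage and density outcomes just described.

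Age must be known at screening because it is an inclusion criterion. Sex must be known because the screening visit includes "a urinary pregnancy test if female".

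**The concern.** HIV status is observed, not assigned, so nothing in the design makes the two groups alike in age or sex on average. Describing the groups in a table shows an imbalance but does not remove it from the estimate. The regression is the adjustment step that the article states, and the variables it names leave out two that are available for every participant.

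What is at stake is the estimated difference in carriage rate, and in density, between PLHIV and controls. If one group contained more women, or were older, and that characteristic were related to carriage, the resulting difference would be counted as an effect of HIV. The direction is unknown: it could inflate the difference or mask it.

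Timing matters too. Terms named before the data are seen carry more weight than terms added after an imbalance appears.

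**Working it through.** **1. The planned difference.** Sample size calculation starts from 50% carriage in controls ("The sample size is based on 50% carriage rate following inoculation in HIV-negative controls") and a 50% greater rate in PLHIV. Read as a relative increase, this is 0.50 × 1.5 = 75%, a difference of 25 points.

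**2. The plan's own figure.** For a two-sided 5% test and 80% power, with mean proportion 0.625:

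n = [1.960 × √(2 × 0.625 × 0.375) + 0.842 × √(0.50 × 0.50 + 0.75 × 0.25)]² / 0.25² = 57.7, so 58 per group without continuity correction.

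With the correction: (57.7 / 4) × [1 + √(1 + 4 / (57.7 × 0.25))]² = 65.4, so 66 per group and 132 in total. This matches the article exactly. The calculation is an unadjusted comparison of two proportions.

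**3. Size of a possible bias.** For a binary covariate whose effect on carriage is the same in both groups:

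bias = (difference between groups in the share with the covariate) × (difference in carriage between its levels).

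The documents give neither factor, so both are assumed for sex:

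- low: 0.10 × 0.05 = 0.5 points, or 0.5 / 25 = 2% of the planned difference
- middle: 0.20 × 0.20 = 4 points, or 16%
- high: 0.30 × 0.20 = 6 points, or 24%

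**4. What that does to the unadjusted test.** With no true HIV effect and 75 per group, a two-sided 5% test would reject in 7.8% of trials at a 4-point bias and 11.4% at 6 points. If the bias instead hid part of a true 50% versus 75% effect, power at 66 per group (no continuity correction) would fall from 85% to 70% at 4 points and 61% at 6 points. These figures illustrate the assumed range. They are not predictions.

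**5. Room in the binary model.** The limiting count is the smaller outcome class, which at the planned rates is non-carriers:

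- 66 per group: 66 × 0.50 + 66 × 0.25 = 33 + 16.5 = 49.5
- 75 per group: 75 × 0.50 + 75 × 0.25 = 37.5 + 18.75 = 56.25

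The model would have five terms: HIV status, natural carriage, antibiotic concentration, age and sex. That leaves 49.5 / 5 = 9.9 to 56.25 / 5 = 11.25 non-carriers per term, which is workable. It counts antibiotic concentration as one term; entering several antibiotics separately would lower the ratio.

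**The case against.** The strongest objection is that the covariate sentence does not close its list. It says that the two variables "will be included as a variable in the regression", not that they are the only ones. Both belong to this particular design: carriage of other serotypes is allowed at entry, and prophylactic antibiotics are allowed in PLHIV. Naming them is compatible with routine demographic terms being left to a full protocol or SAP that is not shown. This stands. A reader might infer that the plan rules out adjustment for age and sex; the text does not support that.

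Second, the design already limits some confounding. Both groups share the 25 to 45 age range. Regular smokers, people in close contact with vulnerable individuals such as children under 5, and people with other immune-impairing conditions are excluded. Exposure is a controlled inoculum. This also stands, but it narrows the gap without closing it: the age range still spans 20 years, and none of these measures balances sex.

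Third, a reader might extend the point to the immune markers. The text does not support that either. Statistical analysis compares colonised with non-colonised participants and makes paired comparisons before and after inoculation. Neither is the PLHIV versus control contrast, and fixed characteristics such as age and sex cancel in a paired comparison.

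Fourth, the documents give no age or sex effect on carriage and no expected imbalance, so every bias figure is assumed. That is correct, and it is why no single figure is offered.

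**Conclusion.** The point holds for the regressions of carriage and carriage density on HIV status. The comparison is not randomised, the article commits to a regression and names two covariates, and it does not name age or sex although both are known at screening. No stated figure is wrong: the 132 reproduces.

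The size cannot be derived from the documents. Under the assumed imbalances and sex effects, the bias runs from a negligible 0.5 points to 6 points, about a quarter of the planned difference. An age imbalance could add to this or offset it. It would be too strong to say that the HIV estimate will be biased: that needs both an imbalance and an association with carriage, and the documents show neither. The narrower conclusion is that the stated covariate set gives no protection against age or sex differences if they occur, and that this is easily put right. The change should be made before analysis.

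**What to change.** In Statistical analysis, extend the covariate sentence so that age (continuous) and sex are pre-specified alongside natural carriage and baseline serum antibiotic concentrations in the regressions comparing carriage and carriage density between PLHIV and HIV-negative controls. If an existing SAP already does this, a statement to that effect is enough.

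The cost is one sentence and two degrees of freedom. Recruitment and the sample size (132 required, 150 recruited) do not change. Age is recorded for eligibility. That sex is held as a data item is inferred from the pregnancy-test rule and should be confirmed.

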### Primary outcomes

Study objective 1:

Rate of solicited and unsolicited adverse events and serious adverse events recorded during scheduled and unscheduled study visitsParticipant satisfaction evaluated with a Likert-style questionnaire on day 25 post-inoculation

Study objective 2:

Pneumococcal carriage density of serotype 6B on days 2, 7, 14, and 21 post-inoculation in PLHIV and HIV-negative controls

Study objective 3:

Immunoglobulin G and A concentrations in nasal fluid or saliva respectively, and in blood plasma at baseline and on days 2, 7, 14, and 21 post-inoculationExploratory longitudinal analysis of immune cell frequencies and cellular activation at nasal mucosa and peripheral blood at baseline and at days 2, 7, 14, and 21 post-inoculation

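### The plan describes carriage rate by an AUC of carriage density and does not separate carriers, so the claim of denser carriage in PLHIV cannot be told apart from the claim of more frequent carriage

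*Protocol article*

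**What the plan says.** All places are in the protocol article.

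- **Study hypotheses:** "PLHIV will exhibit higher carriage rate and density than HIV-negative controls following experimental pneumococcal inoculation". Rate and density are separate claims.
- **Primary outcomes, objective 2:** the only entry is "Pneumococcal carriage density of serotype 6B on days 2, 7, 14, and 21 post-inoculation in PLHIV and HIV-negative controls". It is stated by HIV group, with no restriction to carriers.
- **Statistical analysis:** "Pneumococcal carriage rate will be described by area-under the curve of carriage density over the duration of follow up", and also "as a binary carriage positive (at any time) compared to carriage negative". A density summary is therefore offered as one of two descriptions of rate. The same section does split colonised from non-colonised participants, but only for immune cells and immunoglobulins.
- **Determination of colonisation:** a carrier is defined by "detection of pneumococcus serotype 6B by microbiological culture in nasal wash samples at any of the time points" after inoculation. Density is measured by culture and by molecular methods.
- **Sample size calculation:** "The sample size is based on 50% carriage rate following inoculation in HIV-negative controls" and "a 50% greater carriage rate amongst PLHIV based on community carriage point-prevalence", leading to "132 participants (66 per group) will be required to achieve 80% power with p=0.05".

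**The concern.** An AUC of density can describe how often carriage occurs only if non-carriers are included. By definition they are culture-negative for 6B at all four post-inoculation visits, so their culture density is zero or below detection throughout. At the planned rates, half of the control values and a quarter of the PLHIV values would then be at the floor. A group comparison of such values responds to the share of carriers as well as to how densely carriers carry.

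A significant AUC or by-day difference could be reported as support for the density half of the hypothesis when PLHIV carriers are no denser than control carriers. If PLHIV carriers were in truth less dense, the true direction could be hidden. The distinction matters for the transmission-reservoir argument in the Introduction, which would read differently for more carriers than for denser carriers.

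**Working it through.** **1. Reproduce the plan's own figure.** The inputs are 50% in controls and 0.50 × 1.5 = 75% in PLHIV, with 80% power and alpha 0.05. Two-sided testing is an assumption, because the calculation does not say.

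- Without continuity correction: n = [1.960·√(2·0.625·0.375) + 0.842·√(0.25 + 0.1875)]² / 0.25² = (1.342 + 0.557)² / 0.0625 ≈ 57.7, so 58 per group.
- With continuity correction: n = (57.7/4)·[1 + √(1 + 4/(57.7·0.25))]² ≈ 65.4, so 66 per group.

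The stated 66 is reproduced, which confirms that the planned rates are 50% and 75%. The sample size is not in error.

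**2. What a rank test sees if carriers are equally dense.** Take one PLHIV and one control participant at random, with non-carriers at zero.

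- Only the PLHIV participant carries: 0.75 × 0.50 = 0.375.
- Both carry and the PLHIV participant is denser: 0.75 × 0.50 × ½ = 0.1875.
- Neither carries, a tie counted as half: 0.25 × 0.50 × ½ = 0.0625.

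The sum is 0.625, against 0.5 under no difference. The excess of 0.125 is half the rate difference and does not depend on how density varies among carriers.

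**3. How often this becomes significant.** Simulation with 5,000 runs per setting: carriage 50% and 75%, the same log10-normal density for carriers in both groups, non-carriers at zero. The assumptions from outside the documents are mean log10 density 2.5, SD 0.5 to 1.5, and the choice of test. The table gives the share of trials with two-sided p < 0.05 and PLHIV higher.

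| Test | 66 per group | 75 per group |
|---|---|---|
| Rank test, everyone | 73% | 78–79% |
| t-test on log10(density+1), everyone | 60–82% | 66–86% |
| t-test on untransformed density, everyone | 2–23% | 2–26% |
| t-test on log10 density, carriers only | 2–3% | 2–3% |

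The 2–3% among carriers is the upper tail of a 5% two-sided test. With 50% carriage in both groups, the all-participant rank test also falls to 2.4%. For reference, the carriage-rate comparison itself has about 85% power at 66 per group and 89% at 75 (no continuity correction).

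**4. AUC over days 2, 7, 14 and 21.** Here 3,000 runs per setting assumed that 10% or 30% of carriers clear between visits. The rank test again gave 73% (66 per group) and 78–79% (75 per group). The t-test on the AUC of log10(density+1) gave 46–61% and 52–67%. In a separate run with carriers' log10 AUC centred at 3, a t-test on the untransformed AUC gave 9%, 5% and 2% at SD 0.8, 1.0 and 1.5 (66 per group).

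**5. Opposite truth.** Suppose PLHIV carriers are 0.5 log10 less dense (SD 1, assumed). The rank probability becomes 0.375 + 0.375 × Φ(−0.5/√2) + 0.0625 = 0.375 + 0.375 × 0.362 + 0.0625 ≈ 0.573, still above 0.5. In simulation the all-participant rank test was significant with PLHIV higher in about 32 to 37% of trials.

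**The case against.** The strongest reply is that no section says density is compared over everyone inoculated or that non-carriers count as zero. Density by group could mean density among those colonised. The analysis set, the rule for negative samples, the scale and the test are details that a condensed article may leave to a full protocol or SAP, and neither is shown. This stands: their absence is not the point made here, and the all-participant reading is an inference. It is the natural one, because an AUC used to describe rate needs the non-carriers. What the article does state is that a density measure describes rate, and a later document would have to correct that statement, not merely add to it.

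A reader might also infer that the rate difference alone would usually yield a significant density result. The documents do not support this in general, because no test is named. It holds for a rank test and for most log-scale settings, but not for a t-test on untransformed density or AUC. Zero density for non-carriers is likewise secure only for culture; molecular density may be above zero in a culture-negative participant.

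The yes/no carriage comparison is already planned, so readers would see a rate difference beside the AUC. That helps, but it does not show whether carriers differ in density. Finally, an all-participant density measure is legitimate in its own right, and a carriers-only comparison conditions on something that happens after inoculation. Both points are fair and are kept in the fix.

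**Conclusion.** The concern holds in a limited form. As written, the article treats a density AUC as a description of carriage rate and gives no density comparison among carriers, so the two halves of its first hypothesis cannot be separated. If everyone inoculated is analysed with culture-negative non-carriers at or near zero, the planned rate difference alone yields a significant result of higher density in about 73% (66 per group) to 78% (75 per group) of trials with a rank test. The figure is roughly 46 to 86% with log-scale tests, depending on the assumed SD, clearance and group size, and about 2 to 26% with a t-test on untransformed values. The rank figure barely depends on the assumed density distribution; the others do. All rest on 50% against 75% carriage. At 40% against 60%, the rank test at 66 per group gives about 57%. The simulations leave out the covariates that the plan intends for its regression.

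**What to change.** For objective 2, state a two-part analysis:

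1. 6B carriage yes or no, by the any-visit culture definition, in everyone inoculated.
2. Log10 6B density AUC among 6B carriers, with a stated value for culture-negative visits within carriers. Such visits will occur, because one positive visit is enough to be a carrier.

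Base any conclusion of higher density on part 2. Keep the all-participant AUC if wanted, but label it a combined rate-and-density measure and stop calling it carriage rate. Present both parts together.

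The cost is analysis wording only. The downside is that part 2 is smaller, with about 66 × 0.50 = 33 control and 66 × 0.75 ≈ 50 PLHIV carriers. Because it conditions on a post-inoculation outcome, it should be reported as a descriptive comparison of carriers.

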*Streptococcus pneumoniae* serotype 6B strain BHN418. Inoculation will occur via a P200 micropipette containing 0.1 mL saline and a pre-specified dose of live pneumococcus. The inoculation dose will start at 20 000 colony-forming units per naris (cfu/naris). If a carriage rate of 50% is achieved in the first eight HIV-negative participants inoculated at this dose, all further participants will be inoculated at this dose. If the achieved carriage rate is below 50% then the dose will be escalated to 80 000 cfu/naris for the next eight HIV-negative participants. The dose may be further increased to 160 000 cfu/naris, then 320 000 cfu/naris, until the target carriage rate of 50% in HIV-negative participants is achieved. An adequate carriage rate is required in order to make statistical comparisons between participants, and in order to effectively evaluate vaccines in future studies using the model. Participants living with HIV will undergo the same dose escalation with close adverse event monitoring to establish safety in this population. The participant will be seated in a semi-recumbent position during inoculation. After inoculation, the participant will remain in this position for up to 15 mins and will be observed in the clinic room for 1 hour. Participants will receive a safety-pack including: i) A pocket-sized post-inoculation advice sheet with emergency contact details in English and Chichewa; ii) a digital thermometer and instruction on how to use it; iii) a course of amoxicillin with instructions of if and when to take them; and iv) a power-bank to ensure participants have access to a charged mobile phone to contact the study team if needed.

**
*Sampling visits (study visit 3-6):*
** Participants will attend for sampling visits on days 2, 7, 14, and 21 post-inoculation. At each sampling visit a member of the study team will complete a structured study visit template electronically which includes a wellness-check, a review of symptoms, a review of vital signs, and a review of intervening antibiotic-use. Samples taken during these visits are detailed below.

**
*Exit visit (study visit 7):*

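### Inoculation dose, which the design may raise 16-fold to increase carriage, is not among the named regression variables; naming it is an optional improvement at almost no cost

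*Protocol article*

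**What the plan says.** **Dose.** Under Participant schedule, Inoculation visit (study visit 2), the protocol article says "The inoculation dose will start at 20 000 colony-forming units per naris (cfu/naris"). If the first eight HIV-negative participants reach 50% carriage, "all further participants will be inoculated at this dose". Otherwise the next eight receive 80 000, and the dose may then go to 160 000 and 320 000, "until the target carriage rate of 50% in HIV-negative participants is achieved". For the other group it says: "Participants living with HIV will undergo the same dose escalation with close adverse event monitoring to establish safety in this population". It gives no number of PLHIV per step.

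**Comparison.** The outcome under Primary outcomes for objective 2 is "Pneumococcal carriage density of serotype 6B on days 2, 7, 14, and 21 post-inoculation in PLHIV and HIV-negative controls". Under Statistical analysis, carriage is also summarised as positive at any time or not, and "Pneumococcal carriage rate will be described by area-under the curve of carriage density over the duration of follow up". The Sample size calculation treats this as one comparison of 75 against 75 and does not set the escalation cohorts apart.

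**Adjustment.** Statistical analysis names two variables: "Natural carriage and baseline serum concentrations of commonly used antibiotics (e.g. cotrimoxazole) will be included as a variable in the regression". Dose does not appear there as a covariate, a stratum or a restriction on who is analysed.

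**The concern.** The protocol raises the dose because it expects a higher dose to produce more carriage. If the ladder is climbed and the two groups are spread differently over the doses, part of the raw difference between PLHIV and controls is a dose difference. Fewer PLHIV than controls on the low steps would exaggerate an excess in PLHIV. More PLHIV on the low steps, conceivable where safety is being established in a new population, would hide one. Objective 2 and the first study hypothesis rest on this comparison. Neither named variable stands in for dose.

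**Working it through.** **The plan's own figure.** Inputs from Sample size calculation: 50% carriage in controls, 50% × 1.5 = 75% in PLHIV, 80% power, p = 0.05 (taken as two-sided).

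- Uncorrected: n = [1.96 × √(2 × 0.625 × 0.375) + 0.842 × √(0.25 + 0.1875)]² / 0.25² = 57.7, so 58.
- Continuity-corrected: (57.7/4) × [1 + √(1 + 4/(57.7 × 0.25))]² = 65.4, so 66.

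The stated 66 per group reproduces. It assumes one control rate, 50%, with no spread over doses.

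**Range of doses.** 320 000 / 20 000 = 16. Three failed steps put 3 × 8 = 24 of 75 controls (32%) below the final dose.

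**Chance of escalating.** P(fewer than 4 carriers of 8) is 93/256 = 36% if true carriage at 20 000 is 50%, 48% if it is 45%, and 81% if it is 30%.

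**Size of the shift with no HIV effect.** No dose-response is given, so these curves are assumptions (carriage at 20/80/160/320 thousand):

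- A: 30/40/45/50%
- B: 20/35/45/50%
- C: 10/25/40/50%
- Mild: 45/50/55/60%
- Flat: 50% throughout

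With 8 controls and k PLHIV at each step below the final dose J, 75 per group and the remainder at J:

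expected shift = [(8 − k)/75] × E[ Σ over steps i below J of (p_J − p_i) ]

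For curve C with k = 4, the chances of ending at steps 1 to 4 are 0.005, 0.113, 0.358 and 0.524. The sums are 0, 0.15, 0.45 and 0.75. The expectation is 0.113 × 0.15 + 0.358 × 0.45 + 0.524 × 0.75 = 0.571, and 0.571 × 4/75 = 3.0 points. The same formula gives 0.9 points for A, 1.7 for B and 0.3 for the mild curve. With k = 12 the signs reverse. With k = 8, or with the flat curve, the shift is 0.

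**Error rate and power.** Simulation, 20 000 runs per scenario, 75 completers per group, with 4 of 8 counted as 50%. Values are curves A/B/C. Power is at a PLHIV-to-control rate ratio of 1.5.

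| PLHIV per step | Null shift, points | Null rejection, z-test without dose, % | Power, z-test without dose, % | Power, Mantel-Haenszel by dose, % |
|---|---|---|---|---|
| 4 | +0.9/+1.7/+3.1 | 6.1/6.7/7.4 | 71.8/75.5/78.7 | 66.2/67.1/66.8 |
| 8 | about 0 | 5.1/5.1/4.3 | 68.4/68.3/65.9 | 68.1/68.9/67.3 |
| 12 | −0.8/−1.7/−3.1 | 4.7/4.9/5.7 | 63.9/57.1/42.8 | 68.1/67.1/64.4 |

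Mantel-Haenszel null rejection stays at 4.5 to 5.3%. Logistic regression shows the same pattern. Without dose its power is 70.0/74.0/77.4% for k = 4 and 61.2/54.2/40.0% for k = 12. With a dose factor it is 64.7 to 69.0% over all three values of k. For density (assumed log10 values, normal with mean 3 and SD 1 in carriers, 0 in non-carriers), the rank test has 37.0 to 73.3% power over k = 4 and 12, and the dose-stratified version 57.2 to 60.8%.

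Under the mild curve, logistic power is 83 to 84% with or without dose. Under A to C the adjusted power is below 80% because carriage is lower at the low doses. A dose term does not recover that loss.

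**The case against.** The strongest reply is that nothing here is wrong as written. The article says that two variables will be included, not that they are the only ones, and an article may leave the full covariate list to an analysis plan that is not shown. The natural reading of the PLHIV sentence is that they pass through the same control-driven ladder. If they do so in cohorts of eight, the shift is about 0 and Mantel-Haenszel changes power by only −0.3 to +1.4 points against the z-test. The 4 and 12 per step are invented counts, and every curve is assumed. The 43% figure needs 10% carriage at the starting dose together with over-representation of PLHIV on the low steps. All of this stands, and it sets the weight of the point. What remains is that the article does name adjustment variables and leaves out the one that its own design manipulates.

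Three stronger readings are tempting, and the documents do not support them:

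- **The comparison is biased by design.** Bias needs escalation, dose-dependent carriage and unequal numbers together, and none of these is established.
- **Null rejection could reach 35%.** That figure assumes 24 controls and no PLHIV below the final dose, which contradicts the statement that PLHIV go through the same escalation.
- **The protocol must fix eight PLHIV per step, or drop the eight controls whose result set the final dose.** The first is a design choice to which the article gives a safety purpose. The second matters only for a comparison restricted to the final dose, which the article does not propose.

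**Conclusion.** The point holds as a minor, optional improvement to a stated model. It is neither an error nor a contradiction. Dose may vary 16-fold, the number of PLHIV per dose is not fixed, and dose is not a named variable. With unequal numbers and a steep dose-response, the unadjusted carriage difference moves by about 1 to 3 points in either direction. Unadjusted power (z-test) ranges from 43% to 79%, against 64 to 69% with dose in the analysis; the high end is inflated by the imbalance itself. These sizes rest wholly on the assumed curves and counts. With matched cohorts, with success in the first eight controls, or with carriage unrelated to dose, there is nothing to correct.

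**What to change.** In Statistical analysis, add inoculation dose as a factor in the carriage and density regressions. Equivalently, use Mantel-Haenszel stratified by dose for carriage at any time, and a dose-stratified rank test for density and its area under the curve.

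The cost is one phrase, since the dose given to each participant is known. With matched numbers no power is lost: logistic power is 67 to 69% with dose and 63 to 66% without. With 4 PLHIV per step logistic power falls from 70–77% to 66–67%, but the difference comes from the dose imbalance. If dose is a factor, participants at a dose given to only one group do not contribute to the HIV comparison. Recruitment began in June 2023, so the ladder may already have been climbed; the analysis change can still be made.
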